#### Trial timepoints

Assessment of adverse drug effects will be collected with 4 time points: 0th, 1st, 6th, 12nd weeks of the trial day. The pain symptoms, QoL and diet pattern will be recorded with 3 time points: 0th, 6th, 12nd weeks. The blood collection (3 mL) for pharmacokinetic and pharmacogenetic tests will be performed on 2 time points: 0th, 6th weeks. The blood (10 mL), feces, skin scrapping, and saliva samples will be taken for biochemistry tests (plasma/ serum), microbiome (gut/ skin/ saliva), cytokines (plasma) and bacterial metabolites (serum/ feces) will be analyzed at 2 time points: 0th, 12nd weeks. The overview of the tests and visits of the clinical trial was shown on the following Table 1.

**Table 1 Tab1:** SPIRIT schedule of enrolment and assessments

#	Timepoint	Week-0 baseline	Week-1 follow-up	Week-6 follow-up	Week-12 follow-up
		T1	T2	T3	T4
1	**Enrolment**				
	Eligibility screening	x			
	Informed consent	x			
	Allocation	x			
2	**Assessment**				
	CRF01 Case Record Form^a^	x			
	CRF02 FW & ADR^b^	x	x	x	x
	CRF03 ESAS	x		x	x
	CRF04 EQ-5D-5 L	x		x	x
	CRF05 Food Frequency Questionnaire	x		x	x
3	**Blood Samples, Serum**				
	Blood Chemistry^c^	x			x
	Cytokines^d^	x			x
	Bacterial Metabolites^e^	x			x
	Pharmacokinetics parameters	x		x	
	Pharmacogenetics parameters	x		x	
4	**Feces Samples**				
	Fecal Microbiome Profile	x			x
	Fecal Bile Acid Profile^f^	x			x
	Fecal SCFAs^g^ and BCFAs^h^	x			x
5	**Skin Samples**				
	Skin Microbiome Profile	x			x
6	**Saliva Samples**				
	Oral Microbiome Profile	x			x

^a^Demographic and Epidemiological Factors: age, weight, height, waist circumference, hip circumference, neck circumference, alcohol consumption, smoking status, occupation, monthly income, method of health payment, and highest education

^b^Follow up and adverse drug reaction: vital signs, physical examination, lab results to assess liver, kidney and heart function, pharmacokinetic record form, drug tolerance assessment form, and adverse event assessment form

^c^Blood Chemistry: lipid profile, liver function test (LFT)

^d^Cytokines: interleukin-17, interferon-gamma, Interleukin-10, tumor growth factor-beta

^e^Bacterial Metabolites: lipopolysaccharide binding protein, sCD14 levels, equol, cadaverine

^f^Fecal Bile Acid Profile: chenodeoxycholic acid, deoxycholic acid, lithocholic acid

^g^SCFAs: butyric acid, propionic acid, acetic acid

^h^BCFAs: iso-butyric acid

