#### Quantitative analysis of cytokines and bacterial metabolites

We will assess alterations in various cytokines, bacterial metabolites, and the microbiome. Quantitative measurement of IL-10 and TGF-β as anti-inflammatory cytokines, and IL-17 and IFN-γ as inflammatory cytokines will be conducted with Flow Cytometry analyzer using human essential immune response panel (13-plex). Bacterial markers such as LBP, sCD14, and equol will be detected using ELISA techniques. Bacterial metabolite concentrations, including short-chain fatty acids, bile acids, and cadaverine, will be determined via HPLC. Then, the expression levels of these parameters before and after treatment will be compared to evaluate the efficacy of the treatment.

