#### Microbial abundance and diversity

For the gut, skin, and oral microbiomes, we will compare microbial abundance at the baseline and end of the trial across different treatment arms to investigate how cannabis oil treatment affects pain assessment. The alpha and beta diversity of the microbiota will be analyzed.

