#### Statistical analysis

The data collected from different questionnaires, including case report forms, will be prepared in Microsoft Excel, followed by data cleaning and extraction. The statistical analysis will be performed on an intention-to-treat basis using Stata/MP software version 16.0 (StataCorp 2017, College Station, TX). Descriptive statistics like pair t-tests for before and after-treatment groups will be carried out using mean with standard deviation for normally distributed continuous data and median with interquartile range for non-normal distributed continuous data. Categorical data will be presented as counts and percentages using the Chi-square test. Continuous data will be assessed for normal distribution using a histogram and Shapiro–Wilk test. One-way ANOVA with Bonferroni correction will be used for normally distributed continuous data, and the Kruskal-Wallis test will be used for non-normal distributed continuous data among 3 arms.

To identify the alpha diversity, Shannon’s diversity index is used for evenness and Chao 1 index for the richness of operational taxonomic units (OTUs). The Jaccard dissimilarity index is used to detect beta diversity, and it is statistically described by permutational multivariate analysis of variance using distance matrices (PERMANOVA) test. A statistically significant level is defined as *p* < 0.05. Correction for multiple analyses was not done, but they will not be included in the conclusion of the study as factual findings. Sensitivity analysis using some subgroup to show robustness will be considered if the primary outcome is statistical significance.

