Short-chain fatty acids (SCFAs), such as acetate, propionate, and butyrate, are present in the intestine exceeding the concentration of 100 mM, and they are mainly produced by 2 major gut bacterial phyla: *Bacteroidetes* and *Firmicutes* [35]. And branched chain iso-SCFAs, which play a role in membrane permeability and fluidity [36], will be investigated as bioactive bacterial metabolites in breast cancer. The SCFAs (beneficial) and iso-SCFAs (potentially harmful) will be indicators for microbial dysbiosis and bowel health [37] in participants, pre- and post-cannabis oil treatment. Primary and secondary bile acids will be diagnosed as bioactive bacterial metabolites in breast cancer. From a range of bile acid profile, deoxycholic acid (DCA) and chenodeoxycholic acid (CDCA) at the physiological level leads to significant reductions in cell invasion, migration, adhesion, and survival but not to cytotoxicity or apoptosis [38]. In addition, lithocholic acid (LCA) stimulates oxidative stress in breast cancer patients, which can reduce cancer cell proliferation [39]. Serum cadaverine level is expected to be differentially expressed at the post-treatment stage since it is related to the breast cancer aggressiveness. Focusing on these bacterial metabolites, we anticipate identifying unique expression levels and substantial improvements through breast cancer treatment.

In addition, we expect to understand the kinetic changes of cannabis and identify the genes associated with variations that contribute to both the therapeutic effects and side effects of cannabis oil.

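### The analysis section leaves the marker tests uncorrected and bars them from the conclusions, but the outcome section uses 15 of these markers to judge efficacy

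*Protocol article*

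**What the plan says.** Four statements in the protocol article bear on this point.

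- **Threshold** (Statistical analysis): "A statistically significant level is defined as *p* < 0.05". It is not limited to the primary outcome.
- **Multiplicity** (same section): "Correction for multiple analyses was not done, but they will not be included in the conclusion of the study as factual findings". The section does not say which analyses 'they' are.
- **Tests** (same section): for before and after treatment, "Descriptive statistics like pair t-tests for before and after-treatment groups will be carried out using mean with standard deviation". Among the three arms, "One-way ANOVA with Bonferroni correction will be used for normally distributed continuous data", with the Kruskal-Wallis test for non-normal data.
- **Use of the marker results** (Quantitative analysis of cytokines and bacterial metabolites): "the expression levels of these parameters before and after treatment will be compared to evaluate the efficacy of the treatment".

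The markers are listed in the footnotes to Table 1 under Trial timepoints, for example "Cytokines: interleukin-17, interferon-gamma, Interleukin-10, tumor growth factor-beta". They are secondary outcomes; the one primary outcome is ESAS pain at the last visit. The microbiome, cytokines and metabolites are nevertheless stated aims in the Abstract and in the Summary of the study, and the Conclusions section lists them among what the trial will deliver.

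**The concern.** A result kept out of the conclusions because it is uncorrected cannot also be evidence that the treatment works. The analysis section takes the first position and the outcome section the second. With 'they' undefined, a reader of the final report could not tell whether a significant cytokine or bile acid falls under the limitation or counts as evidence of efficacy.

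This matters because there are many markers and each is tested at 0.05. A few significant changes can be expected by chance, and the efficacy wording invites them to be read as treatment effects. The stake is how far the secondary, mechanistic part of the trial can be trusted. The pain result is not at stake.

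**Working it through.** The article states no family-wise error rate, so there is no figure of its own to reproduce.

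**Step 1: count the markers (Table 1 footnotes).** 4 cytokines + 4 bacterial markers or metabolites + 3 bile acids + 3 short-chain fatty acids + 1 branched-chain fatty acid = 15. Lipids and liver function tests are left out, because the Biochemical assay section treats them as baseline characteristics. The paragraph with the efficacy wording does not name iso-butyric acid, but Table 1 lists it among the fatty acids measured before and after treatment. Without it the count is 14 and little changes: 1 − 0.95^14 = 0.51.

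**Step 2: one three-arm test per marker.** Inputs: α = 0.05 per test (two-sided assumed, as no sidedness is stated), m = 15, no true effect.

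- Independent markers: 1 − (1 − α)^m = 1 − 0.95^15 = 1 − 0.463 = 0.537.
- Expected false positives: 15 × 0.05 = 0.75.
- Equal correlation between all markers (not given in the article, so a range), by simulation. The lower figure treats each marker's test as a single two-sided z-test, the higher one as a three-arm test.

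| Correlation | At least one false positive |
|---|---|
| 0 | 54% |
| 0.3 | 46% |
| 0.5 | 36–37% |
| 0.8 | 20–22% |

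**Step 3: favourable results only.** With half of α in the favourable tail: 1 − 0.975^15 = 1 − 0.684 = 0.316, with 15 × 0.025 = 0.375 expected. This is for independent markers; at correlation 0.5 it falls to 18%.

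**Step 4: the before/after tests that the efficacy sentence refers to.** 15 markers × 3 arms = 45 paired tests, with no true change in any arm.

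- Independent markers: 1 − 0.95^45 = 1 − 0.099 = 0.901.
- Expected false positives: 45 × 0.05 = 2.25.
- Correlation 0.5 between markers, arms independent: 1 − (1 − 0.360)^3 = 1 − 0.262 = 0.738, matching the simulated 73.9%. At correlation 0.3 the simulation gives 84%.

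**Step 5: does the named Bonferroni correction help?** It is attached to the one-way ANOVA among three arms, so it most naturally adjusts the pairwise arm contrasts within one variable. None is named for the Kruskal-Wallis or paired tests, and nothing adjusts across the 15 markers.

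**Step 6: after a correction.** Under Benjamini-Hochberg at 5%, the k-th smallest of the 15 p-values is compared with k × 0.05/15, so a lone signal needs p ≤ 0.0033. If no marker truly changes and the tests are independent, the chance of declaring any finding is then about 5%, against 54% in step 2.

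**The case against.** The strongest defence is the second half of the sentence on correction. These are secondary outcomes, the trial has one primary outcome, and the article discloses that there is no correction and keeps such results out of its conclusions. That is an accepted approach, and had it been followed throughout there would be little to raise. The defence fails only where the outcome section gives the same results an efficacy role.

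Several stronger readings are tempting, but the article does not support them.

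- **That there is no safeguard.** There is one. The problem is that it is contradicted and its scope is undefined.
- **That two uncorrected active-versus-placebo tests per marker make a false positive more likely than not** (76% if independent, 56% at correlation 0.5). The article specifies a three-arm test, with Bonferroni for the ANOVA. For that test the figure passes one half only when markers are close to independent.
- **That taxa are tested one by one and used to judge efficacy.** The section on microbial abundance plans to "compare microbial abundance at the baseline and end of the trial across different treatment arms", and ties this to pain assessment, not to efficacy. The microbiome methods named are diversity indices and PERMANOVA. Neither taxon-level tests nor a number of taxa is given, so any count of false taxa would be guesswork.
- **That the Discussion commits the trial to claims.** The sentence "we anticipate identifying unique expression levels and substantial improvements through breast cancer treatment" states an expectation and sets no decision rule. It shows how results may be read, no more.
- **That the secondary aims yield nothing usable.** Reporting estimates as exploratory remains open.

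**Conclusion.** The point holds as an internal conflict with a measurable consequence. The analysis section bars uncorrected results from the conclusions, and the outcome section uses 15 of these markers to evaluate efficacy. Both cannot stand.

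How likely a chance finding is depends on which tests are counted. For the planned between-arm test it is appreciable but not certain, and a chance result in the favourable direction is less likely still. For the before/after tests on which the efficacy sentence rests, at least one false positive is likely in the range examined for them, independence to correlation 0.5.

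These figures assume two-sided tests, equal correlation between markers and no true change. The last assumption is idealised for the paired tests: all patients are starting or receiving chemotherapy, so markers may move within an arm for reasons unrelated to the oil. That is a further reason to rest any treatment claim on between-arm comparison.

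The primary pain outcome is unaffected. This is an inexpensive improvement, not a flaw that threatens the trial's main result.

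**What to change.** 1. **Quantitative analysis of cytokines and bacterial metabolites:** replace the efficacy wording with an exploratory, mechanistic purpose based on comparing changes between arms. Bring the expectations of improvement in the Discussion into line.
2. **Statistical analysis:** define 'they' as the secondary marker and microbiome analyses.
3. **Statistical analysis:** replace the no-correction rule with text such as: *The between-arm tests of the 15 listed markers form one family, in which the false discovery rate is controlled at 5% by the Benjamini-Hochberg method. If individual taxa are tested, the taxa at each body site form a separate family. Unadjusted estimates with confidence intervals are reported alongside the adjusted p-values.*
4. **Within-arm paired tests:** state that they are descriptive, or include them in the family.

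If the sponsor prefers to leave these tests uncorrected, items 1 and 2 and an exploratory label throughout would remove the contradiction, though the markers could then support only hypotheses.

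The cost is a few wording edits and one added analysis step, with no change to sample size, visits or samples. The downside is fewer nominally significant markers.

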## Discussion

Thailand actively launched cannabis oil in the market in 2018, subsequently, the FDA (Food and Drug Administration) authorized all hospitals running under the Public Health Ministry for medical cannabis to be available on prescription to patients for approved conditions like cancer chemotherapy for relief of pain, to counter inflammation, and so on [32]. The previous clinical trial as nationwide has been approved the effectiveness of the cannabis oil in cancer patients. The current study is a continual clinical trial to obtain additional information and it is expected to improve the chemotherapy-related symptoms, their QoL, and the adverse effects in breast cancer patients.

As some studies have observed distinct gut bacterial and fungal profiles in various breast cancer subtypes [15, 16], our anticipation is to identify a comparable microbial abundance pattern in both hormone-dependent and independent breast cancer patients. Additionally, we aim to detect alterations in these patterns before and after treatment with cannabis oil and placebo oil, with a focus on pain scores. A noteworthy aspect of this study is its comprehensive examination of the microbiota, encompassing the gut, skin, and oral microbiomes in breast cancer patients.

An advantageous aspects of this study are the effective observation of the immunomodulatory role of the microbiota measuring interleukin-17 (IL-17) and interferon-γ (IFN-γ), interleukin-10 (IL-10) and tumor growth factor-β (TGF-β) and the assessment of the alterations at both the baseline and post-treatment stages or within each treatment group. This approach is expected to yield specific insights into cytokine expression in breast cancer patients and reveal improvement following treatment.

The levels of Lipopolysaccharide-binding protein (LBP) and soluble CD14 (sCD14) serve as markers for bacterial translocation, indicating the potential existence of a gut-breast cancer microbiota axis [33]. It is essential to assess the influence of cannabis oil on preventing the bloodstream transmission of oncogenic bacteria through this axis. Additionally, equol, a potent estrogenic metabolite produced by intestinal bacteria [34], Is of interest. The study also aims to establish a distinct profile of bacterial markers in breast cancer patients and gain insights into their characteristics following treatment.

Short-chain fatty acids (SCFAs), such as acetate, propionate, and butyrate, are present in the intestine exceeding the concentration of 100 mM, and they are mainly produced by 2 major gut bacterial phyla: *Bacteroidetes* and *Firmicutes* [35]. And branched chain iso-SCFAs, which play a role in membrane permeability and fluidity [36], will be investigated as bioactive bacterial metabolites in breast cancer. The SCFAs (beneficial) and iso-SCFAs (potentially harmful) will be indicators for microbial dysbiosis and bowel health [37] in participants, pre- and post-cannabis oil treatment. Primary and secondary bile acids will be diagnosed as bioactive bacterial metabolites in breast cancer. From a range of bile acid profile, deoxycholic acid (DCA) and chenodeoxycholic acid (CDCA) at the physiological level leads to significant reductions in cell invasion, migration, adhesion, and survival but not to cytotoxicity or apoptosis [38]. In addition, lithocholic acid (LCA) stimulates oxidative stress in breast cancer patients, which can reduce cancer cell proliferation [39]. Serum cadaverine level is expected to be differentially expressed at the post-treatment stage since it is related to the breast cancer aggressiveness. Focusing on these bacterial metabolites, we anticipate identifying unique expression levels and substantial improvements through breast cancer treatment.

In addition, we expect to understand the kinetic changes of cannabis and identify the genes associated with variations that contribute to both the therapeutic effects and side effects of cannabis oil.

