### Summary of the study

Hence, the current randomized study aims to explore the efficacy of Thai cannabis oil products on the QoL of individuals diagnosed with breast cancer and treated with chemotherapies, along with the study of microbial alteration and diversity by cannabis and pharmacokinetic measures among those patients. We aim to determine the intensity of the pain and QoL experienced by cancer patients using the ESAS and the EQ-5D-5 L forms, respectively, to explore the microbiome profile, cytokines, and bacterial metabolites in hormone-dependent and independent breast cancer patients before and after the treatment with the cannabis oil or no cannabis, and to study the pharmacokinetics parameters and pharmacogenetics profile.

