#### Patient allocation and blinding

The recruited patients will be randomly allocated into 3 groups: Ganja Oil (THC 1.701 mg/mL or 0.068 mg/drop; CBD 0.003 mg/mL or 0.0001 mg/drop; CBN 0.170 mg/mL or 0.007 mg/drop; COA Ganja Oil TRCM65/05232), Metta Osot (THC 77.622 mg/mL or 3.105 mg/drop; CBD 6.737 mg/mL or 0.2695 mg/drop; CBN 7.406 mg/mL or 0.296 mg/drop; COA Metta Osot TRCM64/33,743 Rev.1), and placebo oil (THC 0 mg/mL or 0 mg/drop; CBD 0 mg/mL or 0 mg/drop; CBN 0 mg/mL or 0 mg/drop; COA Placebo TRCM64/33,742) groups. The allocation will be conducted with a 1:1:1 ratio using block randomization with a block of six by the table of random numbers for creating randomization ID. The research team will provide the randomization code in an opaque envelope to conceal allocation, mask clinicians, data collectors, and patients. Following the cannabis practice patterns of the preliminary study [29], all the participants will be received cannabis or placebo oil once per day before bedtime for 12 weeks.

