### Statistical considerations

#### Sample size estimation

We target 30 patients in each arm, considering the maximum follow-up loss of 50%. Since the target population is metastatic breast cancer cases, questionnaires and biological samples such as blood, stool, saliva, and breast skin scrapping will be collected before and after the treatment, which could increase the withdrawal rate at any time during the trial.

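### Two exploratory Discussion statements, and the before-and-after test of marker efficacy, claim more than an oil-versus-placebo trial in women who all have breast cancer can show

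*Protocol article*

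**What the plan says.** Two sentences in the protocol article's Discussion describe what the laboratory markers should show. The first is worded as an aim: "The study also aims to establish a distinct profile of bacterial markers in breast cancer patients and gain insights into their characteristics following treatment". The second, which closes the text on short-chain fatty acids, bile acids and cadaverine, is an expectation: "we anticipate identifying unique expression levels and substantial improvements through breast cancer treatment".

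The methods section on these markers (Quantitative analysis of cytokines and bacterial metabolites) says that "the expression levels of these parameters before and after treatment will be compared to evaluate the efficacy of the treatment". Under Trial timepoints, "cytokines (plasma) and bacterial metabolites (serum/ feces) will be analyzed at 2 time points: 0th, 12nd weeks".

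The objective in Summary of the study is narrower. It is to explore the markers "in hormone-dependent and independent breast cancer patients before and after the treatment with the cannabis oil or no cannabis".

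**The concern.** A marker profile can be called distinct to a disease only against people who do not have it, or against reference values from such people. A change can be credited to a treatment only if some comparable group did not receive that treatment. The Discussion sentences, read at face value, make one claim of each kind, and the design described in the article provides for neither.

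The statement in the methods section matters more in practice, because it says how efficacy will be judged. If a fall in a bacterial translocation marker between week 0 and week 12 within an oil arm is taken as evidence of efficacy, the effect of ongoing chemotherapy and of time could be reported as the effect of the oil. The levels seen in the cohort could likewise be reported as characteristic of breast cancer when they were never compared with anything else.

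**Working it through.** The article states no figure on this point, so the check sets the claims beside the design.

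**Design facts**

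- Population: Inclusion criteria admit only women diagnosed with breast cancer. With 3 × 30 = 90 planned participants, 0 of 90 are without the disease. The article describes no non-cancer sample or reference range.
- Cancer treatment at entry: the same criteria take any stage, and women who are about to start chemotherapy or are already on it, with differing regimens.
- Randomised factor: "The recruited patients will be randomly allocated into 3 groups: Ganja Oil", Metta Osot or placebo oil. The article adds that "The allocation will be conducted with a 1:1:1 ratio using block randomization with a block of six". Cancer treatment is varied by design in 0 of 3 arms.
- Marker sampling: weeks 0 and 12 (Trial timepoints and Table 1).
- Planned tests: Statistical analysis lists paired tests for before and after, and one-way ANOVA or Kruskal-Wallis across the three arms.

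**Claim 1: a profile distinct to breast cancer.** This needs a contrast of women with and without breast cancer. The second group does not exist here, so the contrast is not estimable. The article's own background (Gut microbiota in breast cancer) supports microbial differences with studies that compared patients with healthy individuals, which is the comparator missing here. A contrast between hormonal subtypes is available, because subtype is taken from the medical record (Patient enrollment and recruitment).

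**Claim 2: improvement through breast cancer treatment.** All arms carry background chemotherapy, so no randomised comparison isolates it. Week 0 is not a pre-chemotherapy baseline for women already on treatment, so a change from week 0 to week 12 cannot be read as its effect either.

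**Claim 3: efficacy from before-and-after levels.** As a simple additive sketch:

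- mean change in an oil arm = oil effect + (chemotherapy + time)
- mean change in the placebo arm = (chemotherapy + time)
- difference between the two = oil effect

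Randomisation makes the bracketed term equal in expectation across arms. It cancels only in the between-arm difference and stays in full in each within-arm change. The methods sentence names the before-and-after comparison as the basis for efficacy. The across-arm tests appear elsewhere, and the article does not say that they decide the marker conclusions.

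| Statement | Contrast needed | Available? |
|---|---|---|
| Distinct profile, versus no breast cancer | cancer vs no cancer | No |
| Distinct profile, by subtype | hormone-dependent vs independent | Yes, observational |
| Improvement through cancer treatment | with vs without that treatment | No |
| Effect of the study oil | each oil vs placebo | Yes, randomised |

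**The case against.** The strongest reply is that these are Discussion remarks, not the trial's objectives. Summary of the study and Conclusions promise only marker changes with and without cannabis oil, and Summary of the study adds hormonal subtype. The design can address both. The second sentence is an anticipation, not an aim. The wording also allows milder readings. The Discussion itself uses *distinct* of differences between breast cancer subtypes, and *treatment* in the sentences nearby often means the study oil, for which there is a placebo arm. All of this stands, and it is why the point is minor. It does not remove the need to reword: if the oil was meant, the second sentence misnames the intervention, and if subtype was meant, the first does not say so.

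It can also be said that Statistical analysis already plans across-arm tests and keeps uncorrected multiple analyses out of the factual conclusions. The first is correct, so the fix needs no new comparison, only a statement of which one carries the conclusion. The second concerns multiplicity and does not supply a missing comparator.

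Adjustment for week 0 is an analytic choice that an unseen analysis plan may already contain. That is fair: the essential change is to oil versus placebo, and adjustment is a way to use the week-0 value already collected.

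A reader might go further and infer that the trial's marker aims cannot be answered, that the marker data have no value, or that no result could contradict the statements. The documents do not support this. Every marker remains usable for oil versus placebo, and markers could worsen, stay flat, or move equally on placebo. The missing contrasts are not estimable, which is different from an estimate with poor precision.

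**Conclusion.** The point holds in limited form. A profile distinct from women without breast cancer, and improvement caused by breast cancer treatment, are not estimable from this design. Before-and-after change within an arm is not a sound basis for marker efficacy while chemotherapy continues in every arm.

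It reaches the exploratory laboratory outcomes: the cytokines, LBP, sCD14, equol, cadaverine, the fatty acids and the bile acids. The primary outcome (ESAS pain at the last visit) and the objectives in Summary of the study are unaffected, and no arm, visit, sample or sample size is called into question.

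The conclusion rests on two assumptions. The first is that *distinct* and *breast cancer treatment* are taken at face value; on the milder readings only clarification is needed. The second is that the full protocol, which is not shown, names no non-cancer reference; if it does, the Discussion sentence on a distinct profile should cite it.

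**What to change.** 1. In Quantitative analysis of cytokines and bacterial metabolites, and where the Discussion speaks of marker improvement, base efficacy conclusions on each oil versus placebo at week 12, adjusted for the week-0 value. State that within-arm changes are descriptive.
2. In the Discussion, replace the wording on distinct or unique profiles with a descriptive comparison of hormone-dependent and hormone-independent disease at week 0.
3. Replace the reference to breast cancer treatment with the study oil, or delete it.
4. Add one sentence saying that no conclusion will be drawn about breast cancer versus no breast cancer, or about the effect of chemotherapy.

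The cost is a narrower claim and a few reworded sentences. Table 1 already schedules the week-0 and week-12 samples, so no new data are needed.
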